### **8.3.3 Serious Adverse Event Reporting and Documentation Requirements**

#### **8.3.3.1 Serious Adverse Event Reporting to the Coordinating Center**

Use the UC CCC protocol number and the protocol-specific patient ID assigned during trial registration on all reports.

All serious adverse events (as defined above) occurring on this study require expedited reporting to the University of Chicago Comprehensive Cancer Center (UC CCC).

SAEs will be reviewed by the Lead Principal Investigator, who will determine whether they are SUSARs. The Lead Principal Investigator or designee will report all SUSARs to the UC CRA and UC CCC, who will report simultaneously to the UC IRB, and other US sites according to regulations (see below).

The responsible Research Nurse or other designated individual at the treating site should report the SAE to the Study Lead Investigator, the University of Chicago CRA and the UC CCC Cancer Clinical Trials Office (CCTO) by the end of the business day when s/he becomes aware of the event. Events occurring after business hours should be reported to the CCTO by 12pm (noon) the next business day. Reports should be made using the 'Serious Event Report' Form. Please scan and send via email (preferred) or fax to the following:

University of Chicago Phase II CRA General:

[[contact]](mailto:[contact])

[contact]

UC CCC Cancer Clinical Trials Office Quality Assurance:

[[contact]](mailto:[contact])

All serious adverse events should also be reported to the local IRB of record according to their policies and procedures.

### **8.3.3.2 Serious and Unexpected Adverse Event Reporting by the Coordinating Center**

The designated UC CCC Regulatory Manager will notify all participating sites of all SUSARs that occur on this clinical trial and which are reported to the UC Institutional Review Board (IRB).

### **SAE Reporting by the Lead Principal Investigator to Amgen**

The Lead Principal Investigator must inform Amgen in writing by e-mail or fax at the contact information listed below for all SUSARs that are judged as reasonably related to the Amgen study drug. Site will transmit the final MedWatch form of that event to Amgen within twenty-four (24) hours. A line listing of SAEs should also be submitted to Amgen every 6 to 12 months in accordance with Amgen's SAE reporting requirements.

For regulatory reporting purposes, an event of "Death, Cause Unknown" from the study shall be processed as a SUSAR. All forms must be completed and provided to Amgen in English.

The Individual Case Safety Report (ICSR) may be referred to as an individual safety report or SAE Report, including Pregnancy Exposure Reports and Follow up Reports. The ICSR must be as complete as possible, at a minimum including event reference number, protocol name and number, investigator contact information, specific patient identifiers (e.g., initials, patient number, date of birth or age, or gender), the name of the suspect study drug, the date and dosage(s) of exposure, event, the date(s) of event, country of event, "Serious" criteria, relationship/causality of study drug, hospitalization history for the event, event

status/outcome, relevant history (including diagnostics, laboratory values, radiographs, concomitant medications, and event treatment, and narrative summary.

The Lead Principal Investigator shall be responsible for collecting all SAEs and Pregnancy and Lactation Exposure Reports and will exercise commercially reasonable due diligence to obtain follow-up information on incomplete SAE or Pregnancy and Lactation Exposure Reports. In the event that Amgen requires clarification or further information on individual SAE or Pregnancy and Lactation Exposure Reports, Amgen will not contact non-party investigators directly, but will route all such inquiries through the Lead Principal Investigator for forwarding to such investigator(s). The Lead Principal Investigator will be responsible to ensure such inquiries are completed and provided in a timely manner to Amgen.

Information not available at the time of the initial report (e.g., an end date for the SAE, discharge summaries, lot numbers, relevant laboratory values, scan data and autopsy reports, which are received after the initial report) must be documented on a follow-up form, and submitted to Amgen in the same timelines as outlined above. The Lead Principal Investigator shall be responsible for obtaining follow-up information for the SAEs and demonstrate diligence in attempting to obtain such information by, among other things, maintaining written records of such attempts.

Other aggregate analysis including reports containing safety data generated during the course of the study is to be submitted to Amgen at the time the Lead Principal Investigator submits to anybody governing research conduct i.e. RA, IRB etc. Final study report and reports of unauthorized use of a marketed product to be submitted to Amgen at the time the Lead Principal Investigator ISS submits to anybody governing research conduct i.e. RA, IRB etc. but not later than one calendar year of study completion.

Reports containing safety data generated during the course of the study are to be submitted to Amgen at the time the Lead Principal Investigator submits to anybody governing research conduct, i.e. regulatory authorities and IRBs. The Lead Principal Investigator will support reconciliation of all ICSRs at the end of the study at a minimum.

The Amgen protocol number (**20167943**) and the institutional protocol number should be included on SAE reports to Amgen.

### **SAE Reporting by Lead Principal Investigator to Celgene**

For the purpose of regulatory reporting, Celgene Drug Safety will determine the expectedness of events of being related to lenalidomide based on the Investigator Brochure. In the United States, all suspected unexpected serious adverse reactions (SUSARs) will be reported in an expedited manner in accordance with 21 CFR 312.32.

Serious adverse events (SAE) are defined above. The investigator must inform Celgene in writing using a Celgene SAE form or MEDWATCH 3500A form of any SAE within 24 hours of being aware of the event. The written report must be completed and supplied to Celgene by facsimile within 24 hours. The initial report must be as complete as possible, including an assessment of the causal relationship between the event and the investigational product(s). Information not available at the time of the initial report (e.g., an end date for the adverse event or laboratory values received after the report) must be documented on a follow-up report. A final report to document resolution of the SAE is required. The Celgene protocol number (RV-CL-MM-PI-005610) and institutional numbers should be included on SAE reports to Celgene. A copy of the fax transmission or email confirmation of the SAE report (or on the fax cover letter) sent to Celgene should be attached to the SAE and retained with the patient records.

Participating study sub-sites must report SAEs to Celgene as described and within 24 hours of awareness. Participating sub-sites must also report SAEs to the University of Chicago as described in Section 8.3.3.2.

## **SAE Reporting by the Lead Principal Investigator to Janssen Scientific Affairs, LLC**

### **Overview**

As the sponsor of the study, the Lead Principal Investigator shall be solely responsible for complying, within the required timelines, any safety reporting obligation to competent health authorities, IRB/ECs and any participating (co or sub) investigators, as defined in applicable laws and regulations. For the purposes of this section, safety data includes adverse events, product quality complaints (PQCs), and special situations including pregnancies.

The Lead Principal Investigator will provide safety information to Janssen Scientific Affairs, LLC on adverse events, special situations including pregnancies and product quality complaints as defined within this section. Additionally, MedWatch Forms will be used to report SAEs.

### **Management of Safety Data**

This study has been designated as an interventional study. As such, all adverse events for Janssen medicinal products regardless of causality and special situations excluding those from subjects not exposed to a Janssen medicinal product and product quality complaints with or without an adverse event as described in this section will be reported from the time a subject has signed and dated an informed consent form until completion of the subject's last study-related procedure (which may include contact for follow-up safety). Serious adverse events will be reported for 30 days after the last dose of study drug.

For the purposes of this study, the Janssen medicinal product is: DARZALEX™ (daratumumab)

### **Definitions**

#### **Adverse Events of Special Interest**

Adverse events of special interest are events that Janssen Scientific Affairs, LLC is actively monitoring as a result of a previously identified signal (even if non-serious). These adverse events are:

- Infusion reactions:  $\geq$  Grade 3
- Infections:  $\geq$  Grade 4
- Cytopenias:  $\geq$  Grade 4

- HBV reactivation
- Other malignancies

Any adverse event of special Interest that is to be reported to Janssen should be recorded on a Serious Adverse Event Report Form and be reported to Janssen within 24 hours of knowledge of the event.

### **Individual Case Safety Report (ICSR)**

A valid ICSR must contain the four minimum criteria required to meet regulatory reporting requirements.

- an identifiable subject (but not disclosing personal information such as the subject's name, initials or address)
- an identifiable reporter (investigational site)
- a Janssen medicinal product
- an adverse event, outcome, or certain special situations

The minimum information required is:

- suspected Janssen medicinal product (doses, indication)
- date of therapy (start and end date, if available)
- batch or lot number, if available
- subject details (subject ID and country)
- gender
- age at AE onset
- reporter ID
- adverse event detail (AE verbatim in English), onset date, relatedness, causality, action taken, outcome, (if available)
- Janssen protocol ID

### **Product Quality Complaint (PQC)**

A product quality complaint is defined as any suspicion of a product defect related to a potential quality issue during manufacturing, packaging, release testing, stability monitoring, dose preparation, storage or distribution of the product, or delivery system. Not all PQCs involve a subject. Lot and batch numbers are of high significance and need to be collected whenever available.

Examples of PQC include but not limited to:

- Functional Problem: e.g., altered delivery rate in a controlled release product
- Physical Defect: e.g. abnormal odor, broken or crushed tablets/capsules
- Potential Dosing Device Malfunction: e.g., autoinjector button not working, needle detaching from syringe
- Suspected Contamination
- Suspected Counterfeit

\*Medical and scientific judgment should be exercised in deciding whether expedited reporting is also appropriate in other situations, such as important medical events that may not be immediately life threatening or result in death or hospitalization but may jeopardize the subject or may require intervention to prevent one of the other outcomes listed in the definition above. These should usually be considered serious and should be reported using a MedWatch Form.

NOTE: DEATH FOR ANY REASON SHOULD BE REPORTED AS A SERIOUS ADVERSE EVENT.

### **Hospitalization**

For reports of hospitalization, it is the sign, symptom or diagnosis which led to the hospitalization that is the serious event for which details must be provided.

Any event requiring hospitalization or prolongation of hospitalization that occurs during the study must be reported as a serious adverse event, except hospitalizations for the following:

- Hospitalizations not intended to treat an acute illness or adverse event (e.g., social reasons such as pending placement in long-term care facility)
- Surgery or procedure planned before entry into the study. [Note: Hospitalizations that were planned before the start of data collection and where the underlying condition for which the hospitalization was planned has not worsened will not be considered serious adverse events. Any adverse event that results in a prolongation of the originally planned hospitalization is to be reported as a new serious adverse event.]

- [For convenience the investigator may choose to hospitalize the subject for the duration of the treatment period.]

### **Life-Threatening Conditions**

Disease progression should not be recorded as an adverse event or serious adverse event term; instead, signs and symptoms of clinical sequelae resulting from disease progression/lack of efficacy will be reported if they fulfill the serious adverse event definition.

### **Unlisted (Unexpected) Adverse Event/Reference Safety Information**

An adverse event is considered unlisted if the nature or severity is not consistent with the applicable product reference safety information. For a medicinal product(s) with a marketing authorization, the expectedness of an adverse event will be determined by whether or not it is listed in the applicable product information.

<http://www.darzalex.com/shared/product/darzalex/darzalex-prescribing-information.pdf>

For DARZALEX™ (daratumumab), the expectedness of an adverse event will be determined by whether or not it is listed in the Investigator's Brochure

### **Special Reporting Situations**

Safety events of interest for a Janssen medicinal product that require expediting reporting and/or safety evaluation include, but are not limited to:

- Drug exposure during pregnancy (maternal and paternal)
- Overdose of a Janssen medicinal product
- Exposure to a Janssen medicinal product from breastfeeding
- Suspected abuse/misuse of a Janssen medicinal product
- Inadvertent or accidental exposure to a Janssen medicinal product
- Any failure of expected pharmacological action (i.e., lack of effect) of a Janssen medicinal product
- Medication error involving a Janssen medicinal product (with or without patient exposure to the Janssen medicinal product, e.g., name confusion)

- Suspected transmission of any infectious agent via administration of a medicinal product
- Unexpected therapeutic or clinical benefit from use of a Janssen medicinal product

These safety events may not meet the definition of an adverse event; however, from a Janssen Scientific Affairs, LLC perspective, they are treated in the same manner as adverse events. Special situations should be recorded on the Adverse Event page of the CRF.

Any special situation that meets the criteria of a serious adverse event should be recorded on a Serious Adverse Event Report (or MedWatch) Form and be reported to Janssen Scientific Affairs, LLC within 24 hours of becoming aware of the event.

### **Maintenance of Safety Information**

All safety data should be maintained in a clinical database in a retrievable format. The Lead Principal Investigator shall provide all adverse events, both serious and non-serious, in report format. However, in certain circumstances more frequent provision of safety data may be necessary, e.g. to fulfill a regulatory request, and as such the data shall be made available within a reasonable timeframe at Janssen Scientific Affairs, LLC request.

### **Procedures for Reporting Safety Data and Product Quality Complaints (PQCs) for Janssen Medicinal Products to Janssen Scientific Affairs, LLC**

All adverse events and special situations, whether serious or non-serious, related or not related, following exposure to a Janssen medicinal product are to be documented by the investigator and recorded in the CRF and in the subject's source records. Investigators must record in the CRF their opinion concerning the relationship of the adverse event to a Janssen medicinal product.

All (serious and non-serious) adverse events reported for a Janssen medicinal product should be followed-up in accordance with clinical practice.

### **SAEs and Special Reporting Situations**

All serious adverse events that have not resolved by the end of the study, or that have not resolved upon discontinuation of the subject's participation in the study, must be followed until any of the following occurs:

- The event resolves
- The event stabilizes
- The event returns to baseline, if a baseline value/status is available
- The event can be attributed to agents other than the study drug or to factors unrelated to study conduct
- It becomes unlikely that any additional information can be obtained (subject or health care practitioner refusal to provide additional information, lost to follow-up after demonstration of due diligence with follow-up efforts)

The Lead Principal Investigator will transmit all SAEs and special situations following exposure to a Janssen product under study in a form provided by Janssen Scientific Affairs, LLC in accordance with Section 10, Transmission Methods, in English within 24-hours of becoming aware of the event(s).

In the event the study is blinded, the Lead Principal Investigator will submit an unblinded SAE or pregnancy exposure report to Janssen Scientific Affairs, LLC.

All follow-up information for serious adverse events that are not resolved at the end of the study or by the time of patient withdrawal must be reported directly by the Lead Principal Investigator, within 24 hours becoming aware, to Janssen Scientific Affairs, LLC using the Janssen Scientific Affairs, LLC Serious Adverse Event Report.

All available clinical information relevant to the evaluation of a related SAE, serious ADR or special situation is required.

- The Lead Principal Investigator is responsible for ensuring that these cases are complete and if not are promptly followed-up. A safety report is not considered complete until all clinical details needed to interpret the case are received. Reporting of follow-up information should follow the same timeline as initial reports.

- Copies of any and all relevant correspondences with regulatory authorities and ethics committees regarding any and all serious adverse events, irrespective of association with the Janssen Product under study, are to be provided to Janssen Scientific Affairs, LLC using a transmission method in Section 10 from this Exhibit within 24 hours of such report or correspondence being sent to applicable health authorities.

### **Non-Serious AEs**

All non-serious adverse events should be reported to Janssen Scientific Affairs, LLC according to the timeframe outlined in the Research Funding Agreement section entitled Reporting of Data.

### **PQC Reporting**

A PQC may have an impact on the safety and efficacy of the product. Timely, accurate, and complete reporting and analysis of PQC information from studies are crucial for the protection of patients, investigators, and Janssen Scientific Affairs, LLC, and are mandated by regulatory agencies worldwide. Janssen Scientific Affairs, LLC has established procedures in conformity with regulatory requirements worldwide to ensure appropriate reporting of PQC information. Lot and/or Batch #s shall be collected on any reports failure of expected pharmacological action (i.e., lack of effect). The product should be quarantined immediately and if possible, take a picture.

All initial PQCs involving a Janssen medicinal product under study must be reported to Janssen Scientific Affairs, LLC by the Lead Principal Investigator within 24 hours after being made aware of the event. The Janssen contact will provide additional information/form to be completed.

If the defect for a Janssen medicinal product under study is combined with either a serious adverse event or non-serious adverse event, the Lead Principal Investigator must report the PQC to Janssen Scientific Affairs, LLC according to the serious adverse event reporting timelines. A sample of the suspected product should be maintained for further investigation if requested by Janssen Scientific Affairs, LLC.

### **Reporting Procedures for Reporting Safety Data and Product Quality Complaints (PQCs) for Non-Janssen Medicinal Products**

For SAEs, special reporting situations and PQCs following exposure to a non- Janssen medicinal product under study, the Lead Principal Investigator should notify the appropriate regulatory/competent authority or the manufacturer of that medicinal product (in the absence of appropriate local legislation) as soon as possible.

## **Transmission Methods**

The following methods are acceptable for transmission of safety information to Janssen Scientific Affairs, LLC:

- Electronically via Janssen SECURE Email service (preferred)
- For business continuity purposes, if SECURE Email is non-functional
- Facsimile (fax), receipt of which is evidenced in a successful fax transmission report
- Telephone (if fax is non-functional)

Please use the contact information and process information provided by Janssen Scientific Affairs, LLC.

### **8.3.4 Pregnancy Reporting**

Pregnancy of a female subject or the female partner of a male subject occurring while the subject is on treatment or within 4 weeks after the subject's last dose of study drug are considered expedited reportable events. Study drugs—lenalidomide, dexamethasone, carfilzomib, and daratumumab—are to be discontinued immediately. The pregnancy must be reported within 24 hours of the treating investigator's knowledge of the pregnancy by phone and facsimile using the SAE form to the University of Chicago CRA either by fax or by email. The treating investigator must inform the University of Chicago in writing by email or facsimile of any pregnancy within 24 hours / 1 business day at the latest on the following workday of being aware of the event. The University of Chicago must report pregnancy as an SAE directly to Amgen, Janssen, and Celgene using expedited reporting procedures listed in Section 8.3.3 and 8.3.3.2.

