#### **Pregnancy Reporting by Lead Principal Investigator to Celgene**

For lenalidomide pregnancies and suspected pregnancies (including a positive pregnancy test regardless of age or disease state) of a female subject occurring while the subject is on lenalidomide, or within 28 days of the subject's last dose of lenalidomide, are considered immediately reportable events. Lenalidomide is to be discontinued immediately and the subject instructed to return any unused portion of the lenalidomide to the investigator. The pregnancy, suspected pregnancy, or positive pregnancy test must be reported to the Lead Principal Investigator who will inform Celgene immediately using the Pregnancy Reporting Form provided by Celgene or an approved equivalent form. The exposure of any pregnant female (e.g., caregiver or pharmacist) to lenalidomide is also an immediately reportable event.

The female subject should be referred to an obstetrician-gynecologist, preferably one experienced in reproductive toxicity for further evaluation and counseling.

The Lead Principal Investigator will follow the female subject until completion of the pregnancy, and must notify Celgene immediately about the outcome of the pregnancy (either normal or abnormal outcome).

If the outcome of the pregnancy was abnormal (e.g., spontaneous or therapeutic abortion), the Investigator should report the abnormal outcome as an AE. If the abnormal outcome meets any of the serious criteria, it must be reported as an SAE within 24 hours of the investigator's knowledge of the event using the SAE Report Form, or MedWatch Form.

All neonatal deaths that occur within 28 days of birth should be reported, without regard to causality, as SAEs. In addition, any infant death after 28 days that the Investigator suspects is related to the in utero exposure to the lenalidomide should also be reported within 24 hours of the investigator's knowledge of the event using the SAE Report Form, or approved equivalent form.

If a female partner of a male subject taking investigational product becomes pregnant, the male subject taking IP should notify the investigator, and the pregnant female partner should be advised to call their healthcare provider immediately.

If a pregnancy related event is reported in a female partner of a male subject, the investigator should ask if the female partner is willing to share information with Celgene Drug Safety and allow the pregnancy related event to be followed up to completion.

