The Lead Principal Investigator will inform Celgene immediately, using the Pregnancy Reporting Form provided by Celgene or an approved equivalent form, of any information related to pregnancies or suspected pregnancies (including a positive pregnancy test regardless of age or disease state) occurring in partner of patients while the patients are still treated with lenalidomide or within 28 days of the Patients' last dose of lenalidomide.

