### **1.3.2. Male Subjects**

Male subjects must practice complete abstinence (True abstinence is acceptable when this is in line with the preferred and usual lifestyle of the subject. Periodic abstinence [e.g. calendar, ovulation, symptothermal or post-ovulation methods] and withdrawal are not acceptable methods of contraception.) or agree to use a condom during sexual contact with a pregnant female or a FCBP while taking lenalidomide, during dose interruptions and for at least 28 days after the last dose of lenalidomide, even if he has undergone a successful vasectomy.

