### **1.5.2.2. Male Subjects**

- Must practice complete abstinence (True abstinence is acceptable when this is in line with the preferred and usual lifestyle of the subject. Periodic abstinence [e.g. calendar, ovulation, symptothermal or post-ovulation methods] and withdrawal are not acceptable methods of contraception.) or use a condom during sexual contact with a pregnant female or a FCBP while taking lenalidomide, during dose interruptions and for at least 28 days after the last dose of lenalidomide, even if he has undergone a successful vasectomy.
- Must not donate semen or sperm while receiving lenalidomide, during dose interruptions or for at least 28 days after the last dose of lenalidomide.
- Counseling about pregnancy precautions and the potential risks of fetal exposure must be conducted at a minimum of every 28 days.

- If pregnancy or a positive pregnancy test does occur in the partner of a male subject while taking lenalidomide, the Investigator must be notified immediately.

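### Minor: Section 8.3.4's order to stop all four drugs also catches a man whose partner is pregnant, and Section 6.6 removes a patient on suspicion where Appendix 7 only interrupts lenalidomide

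*Protocol*

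**What the plan says.** **Partner pregnancy.** Section 8.3.4 covers, in a single trigger, "Pregnancy of a female subject or the female partner of a male subject occurring while the subject is on treatment" or within four weeks after the last dose. The sentence that follows names lenalidomide, dexamethasone, carfilzomib and daratumumab and says they "are to be discontinued immediately".

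Appendix 7 handles men separately. Its Section 1.5.2.2 says: "If pregnancy or a positive pregnancy test does occur in the partner of a male subject while taking lenalidomide, the Investigator must be notified" immediately. The same section, and Section 1.3.2, require a man to abstain or "use a condom during sexual contact with a pregnant female or a FCBP while taking lenalidomide". The Celgene reporting section says: "If a female partner of a male subject taking investigational product becomes pregnant, the male subject taking IP should notify the investigator". It also has the Lead Principal Investigator inform Celgene of pregnancies "occurring in partner of patients while the patients are still treated with lenalidomide". The Janssen section asks for reporting and follow-up of partner pregnancies.

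**Suspected pregnancy.** Section 6.6 lists a suspected or positive pregnancy among the reasons for which patients are removed from further treatment, and gives no way back if pregnancy is ruled out. The Celgene section, for known or suspected pregnancy of a female subject (a positive test included), says: "Lenalidomide is to be discontinued immediately and the subject instructed to return any unused portion of the lenalidomide to the investigator". Appendix 7, Section 1.5.2.1, has two rules. Pregnancy or a positive test means immediate discontinuation of lenalidomide. A missed period, or an abnormal test or bleeding, means testing and counselling, with lenalidomide stopped during that evaluation.

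**The concern.** An order to stop treatment has to say whom it applies to and whether it is final. Section 8.3.4 leaves the first open and Section 6.6 the second. A site that follows the words takes a man off a full first-line myeloma regimen for an event in his partner, or permanently removes a woman whose missed period proves to have another cause. A site that follows Appendix 7 does neither. Patients in the same situation could therefore be treated differently according to which page was consulted. What is at stake is treatment for an individual patient and consistency across sites, not the primary test.

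**Working it through.** No arithmetic applies. The check is to set the rules side by side.

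| Situation | Section 8.3.4 | Section 6.6 | Celgene reporting section | Appendix 7 (lenalidomide only) |
|---|---|---|---|---|
| Pregnancy of a female subject | Stop all four drugs | Remove from treatment | Stop lenalidomide at once | Stop lenalidomide at once |
| Suspicion only, female subject | Not addressed | Remove from treatment | Stop lenalidomide at once | Stop lenalidomide during evaluation |
| Pregnancy of a male subject's partner | Stop all four drugs, if read literally | Partner not mentioned | Notify and report | Notify; condom or abstinence |

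**Row 1** is consistent: each rule stops treatment, and they differ only in which drugs they cover.

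**Row 3, partner pregnancy.** Section 8.3.4 is the only place that orders a stop. Appendix 7 draws the distinction itself: Section 1.5.2.1 ties the lenalidomide stop to pregnancy in a subject, and Section 1.5.2.2 ties notification to pregnancy in a partner. Section 1.3.2 has a man "agree to use a condom during sexual contact with a pregnant female or a FCBP while taking lenalidomide", so it foresees a man on lenalidomide whose partner is pregnant. The Celgene and Janssen sections add only reporting and follow-up and are silent on whether he continues. The defect therefore lies in the unlimited stop sentence of Section 8.3.4.

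**Row 2, suspicion.** Removal from further treatment and a stop during evaluation are different instructions. The Celgene section's immediate stop does not settle the matter, because it fits either a hold or a removal. The conflict is between Section 6.6 and Section 1.5.2.1 of Appendix 7.

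**What a hold would meet elsewhere in the Protocol:**

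- Missed carfilzomib doses are not replaced within a cycle (Section 6.3.1).
- A within-cycle daratumumab dose counts as missed, and is not made up, after more than 3 days in Cycles 1 and 2 or more than 7 days later (Section 6.5.1.1 and Table 6-5).
- Daratumumab holds of more than 14 days for reasons other than toxicity are discussed with the Lead Principal Investigator (text under Table 6-5).
- A treatment delay of more than 21 days means removal unless the Lead Principal Investigator approves (Section 6.6).
- Section 6.4 starts the next cycle one dose level lower if a drug was held for the rest of the previous cycle. It is unclear whether the reference to residual toxicity in that sentence limits this case, so a suspicion that is ruled out could still cost a dose level.

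**The case against.** The strongest reply on the partner point is that silence is not contradiction. The supplier sections deal with reporting, Section 6.6 does not mention partners, and the stop sentence was probably meant for women. That stands in part. A reader might infer that the Protocol elsewhere says the man continues; it does not. Appendix 7 covers lenalidomide only, and its precautions imply that he may still be taking the drug without saying so for the regimen. But a probable intention does not limit a sentence that directly follows a trigger naming the partner.

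On suspicion, stopping a teratogenic regimen at once is sound, and both Section 6.6 and the Celgene section do so. Section 6.6 also has the Lead Principal Investigator contacted before any discontinuation. A reader might infer that stopping on suspicion is itself the error; the documents do not support that. What remains is that Section 6.6 makes the stop a removal, while Appendix 7 treats it as temporary for lenalidomide.

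A third reply is that letting a man continue is a safety decision. That is fair: Appendix 7, Section 1.2.3, reports traces of lenalidomide in semen, and the Janssen section says its product's effect on sperm is unknown. The main text (Section 5.1, criterion 14, and Section 6.2.2.1) asks men for two contraceptive methods until 90 days after treatment or study discontinuation, while Appendix 7 asks for a condom or abstinence until 28 days after the last lenalidomide dose. The correction must keep the stricter rule in force.

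**Conclusion.** The point holds as a minor one, on both parts. Section 8.3.4 orders a full-regimen stop without limiting it to a pregnant subject, where Appendix 7 attaches only notification and precautions to a partner's pregnancy. Section 6.6 removes a patient on suspicion, where Appendix 7 interrupts lenalidomide during evaluation.

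The number affected should be small. The Protocol gives no expected count, its contraception and pregnancy-testing rules make the event unlikely, and Section 6.3.5 says there will be no new starts. No sample size, power, significance level or response rate changes. The conclusion assumes that sites apply the sentences as written. If they already read Section 8.3.4 as meaning female subjects and treat suspicion as a hold, the edits only record that practice.

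**What to change.** **Section 8.3.4.** Limit the stop sentence to pregnancy of a female subject. Add that a partner's pregnancy triggers reporting and follow-up, and that both the main-text contraception rules (two methods, 90 days) and the Appendix 7 condom or abstinence precautions continue to apply. If the sponsor does want the man's drugs stopped, it should say so expressly and bring Appendix 7 into line.

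**Section 6.6.** Replace the pregnancy item with wording such as: *Confirmed pregnancy; for a suspected pregnancy or a positive test, all study drugs are stopped immediately pending evaluation and may resume if pregnancy is excluded.* Treating a positive test this way keeps the immediate stop and gives a woman with a false-positive result a way back. Add that such a hold is not a toxicity hold, so the one-level decrement in Section 6.4 does not apply, and that doses missed meanwhile are not made up.

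The Celgene section and Appendix 7 can stay as they are, since an immediate stop is compatible with a hold.

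The cost is wording in two sections, which can go into the next amendment. Section 13.3 already requires consideration of Amgen, Janssen and Celgene before submission, which gives the suppliers the chance to comment on the partner rule. No visits or tests beyond those already required are added.
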